**Target Trial Emulation**

| **(A) Research Question** | ***What is the causal effect of exposure to nifedipine on adverse maternal and neonatal outcomes, compared with exposure to labetalol?*** | |
| --- | --- | --- |
|  | **Target Trial (Giant PANDA)** | **Emulation** |
| **(B) Populations** | All women with hypertensive disorders of pregnancy (chronic hypertension, gestational hypertension, or preeclampsia) requiring antihypertensive medication at gestational age 11^+0^-19^+6^; 20^+0^-27^+6^; and 28^+0^-36^+6^.  *Exclusions:* contraindication to labetalol or nifedipine; on both labetalol and nifedipine prior to randomization; unable to provide informed consent; unable to be randomized. | All women with hypertensive disorders of pregnancy (gestational hypertension, chronic hypertension, or preeclampsia) requiring antihypertensive treatment (dispensed labetalol or nifedipine) between 11^+0^ and 36^+6^ weeks’ gestation.  *Exclusions:* Taking both labetalol and nifedipine prior to 11 weeks’ gestation. |
| **(C) Treatment strategies** | Primary  Intention-to-treat (ITT): All women randomized to labetalol or nifedipine, regardless of discontinuation or crossover of treatment groups.    Sensitivity  Per-protocol: All women randomized to labetalol or nifedipine, who continued with assigned treatment until no longer indicated.  On-treatment: All women randomized to labetalol or nifedipine, who continued with assigned treatment until no longer indicated and who self-reported ≥90% adherence across all study contacts. | Primary  Intention-to-treat (ITT): All women who received ≥1 prescription and dispensation of labetalol or nifedipine, including those who received both medications during the study period (crossover will be determined by timing of dispensation) and those who discontinued treatment.  *Crossover defined as receiving both labetalol and nifedipine between 11-36 weeks’ gestation.*  Sensitivity  Per-protocol: All women who received ≥1 prescription and dispensation of labetalol or nifedipine during the study period, but did not receive both medications at any time. |
| **(C) Assignment procedures** | Randomized at diagnosis of hypertension requiring medical intervention (1:1 ratio of nifedipine/labetalol). | “Randomized” (via inverse probability weighting) at point of first dispensation of labetalol or nifedipine during the study period (≥11 weeks’ gestation and ≤36+6 weeks’ gestation). |

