| **(D) Follow-up period** | From 11 weeks’ gestation until 28 days post-birth. | From 11 weeks’ gestation until 28 days post-birth. |
| **(E) Outcomes** | **Primary Maternal**  Severe hypertension (systolic blood pressure ≥160mmHg).  **Primary Neonatal**  Composite of stillbirth, neonatal death (until 28 days post-birth), and NICU admission requiring separation of infant and mother (until 28 days post-birth).  **Secondary Maternal**  *Note: Variables denoted with a * are reported with treatment effect and 95% CI, all others are exploratory only and described with summary statistics*.   - Mean antenatal systolic blood pressure* - New diagnosis of preeclampsia* - Severe maternal morbidity (fullPIERS consensus definition)* - Discontinuation of allocated antihypertensive* - Undesirable effects of allocated antihypertensive* - Maternal death* - Indicated birth (induction of PROM)* - Mean antenatal diastolic blood pressure - Proportion of days with antenatal systolic blood pressure ≥140mmHg - Proportion of days with antenatal diastolic blood pressure ≥90mmHg - Diagnosis of eclampsia - Diagnosis of HELLP syndrome - Placental abruption - Components of severe maternal morbidity - Maternal stroke - Prescription of additional antihypertensive drugs - Prescription of alternative antihypertensive drugs - Time from randomization to first discontinuation of allocated antihypertensive - Total number of antenatal hospital inpatient days - Treatment satisfaction - Beliefs about allocated antihypertensive drug - Adherence to allocated antihypertensive drug - Mode of onset of birth   **Secondary Neonatal**  *Note: Variables denoted with a * are reported with treatment effect and 95% CI, all others are exploratory only and described with summary statistics*.   - Major congenital anomaly (as defined by EURO-CAT)* - Birthweight centile* - Need for treatment for neonatal hypoglycemia* - Neonatal unit admission (separation of baby from mother)* - Mode of birth* - Gestational age at birth* - Fetal loss <24^+0^ weeks’ gestation - Fetal loss ≥24^+0^ weeks’ gestation (stillbirth) - Known early neonatal death (up to 7 days post-birth) - Known late neonatal death (7-28 days post-birth) - Principal recorded indication for neonatal unit admission - Length of stay in neonatal unit (and level of care) - Indication for mode of birth - Preterm birth (<37 completed weeks) - Preterm birth (<32 completed weeks) - Birthweight - Birthweight SGA (<10^th^ centile) - Umbilical arterial pH<7 at birth - Apgar score 5min post-delivery - Need for additional resuscitation at birth - Need for respiratory support - Type of respiratory support needed - Type of treatment for hypoglycemia - Lowest blood glucose measurement within 48 hours post-birth - Intracranial hemorrhage - Neonatal seizures - Necrotizing enterocolitis | **Primary Maternal**  Our primary outcome will be a composite of severe maternal morbidity determined by an expert panel, comprising:   - Maternal mortality (all cause) - Eclampsia - HELLP syndrome - Stroke - Cortical blindness - Retinal detachment - Pulmonary oedema - Placental abruption - Liver rupture - Need for dialysis - Need for extracorporeal membrane oxygenation (ECMO)   *Note: We do not have reliable ascertainment of ICU/HDU admission data. By instead including only severe morbidities which can reasonably be attributed to hypertensive disorders, we will provide a more accurate picture of the effect of disease-modifying drugs.*  **Primary Perinatal**  Our primary perinatal outcome will be a composite outcome determined by expert consensus. This will comprise.   - Stillbirth (fetal death ≥20 weeks’ gestation) - Neonatal death (death within 28 days of birth) - Severe neonatal morbidity, including:   - Bacterial sepsis   - Birthweight < 3^rd^ centile   - Cardiac arrest   - Hypoxic-ischemic encephalopathy (HIE)   - Intracranial hemorrhage   - Necrotizing enterocolitis   - Neonatal asphyxia   - Neonatal seizures   - Requirement for intubation or mechanical ventilation   - Requirement for resuscitation (mechanical or non-mechanical)   *Note: We do not have reliable ascertainment of NICU admission data. Many infants who are born following hypertensive pregnancies will be admitted to NICU without any other severe morbidities. By instead including only diagnosed severe morbidities, we will provide a more accurate picture of the effect of disease-modifying drugs.*  **Secondary Maternal**  *Note: Variables denoted with a * are reported with treatment effect and 95% CI, all others are exploratory only and described with summary statistics*.   - Pregnancy prolongation (time from first antihypertensive dispensation to birth)* - Need for additional antihypertensive(s)* - Individual components of the primary composite outcome - Disease progression (new diagnosis of preeclampsia after randomization)   **Secondary Perinatal**  *Note: Variables denoted with a * are reported with treatment effect and 95% CI, all others are exploratory only and described with summary statistics*. *** Indicates core secondary outcome.*   - Preterm birth (<37; <34; <32; and <28 weeks’ gestation)** - Major congenital anomaly (as defined by EURO-CAT)* - Neonatal hypoglycemia* - Respiratory distress - Neonatal hypothermia - Individual components of primary composite outcome - Birthweight <10^th^ centile |

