**Define treatment strategy (exposure), assignment procedures, and follow-up period.**

1. The target trial would randomize at the point of diagnosis of a hypertensive disorder of pregnancy (chronic hypertension, gestational hypertension, or preeclampsia). Women would be randomized in a 1:1 ratio to either labetalol or nifedipine. Follow-up would be until 28 days postpartum, and reasons for drop out would include non-adherence to medication, failure to provide consent, unplanned crossover of participants, and random loss to follow up.
2. In the emulated trial, women will be ‘randomized’ at the point of first dispensation of either labetalol or nifedipine at or beyond 11 weeks’ gestation. We will exclude women who were taking both medications prior to 11 weeks’ gestation (unable to be randomized). We will exclude hypertensive women who received neither labetalol or nifedipine (contraindication or non-indication; this cohort will be described). We will also exclude women without hypertension who received labetalol or nifedipine (this cohort will be described).

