**Outcome definitions – primary and secondary outcomes.**

1. In the target trial, the **primary maternal outcome** is severe hypertension (systolic blood pressure ≥160mmHg). We do not have reliable access to blood pressure measurements; however, our much larger sample size allows us to investigate downstream effects of severe hypertension (severe morbidity). Therefore, the primary maternal outcome will be a composite comprising:
   1. Maternal mortality (all cause) (yes/no)
   2. Eclampsia (yes/no)
   3. HELLP syndrome (yes/no)
   4. Stroke (yes/no)
   5. Cortical blindness (yes/no)
   6. Retinal detachment (yes/no)
   7. Pulmonary oedema (yes/no)
   8. Placental abruption (yes/no)
   9. Liver rupture (yes/no)
   10. Need for dialysis (yes/no)
   11. Need for extracorporeal membrane oxygenation (ECMO) (yes/no)
2. In the target trial, the **primary perinatal outcome** is a composite of stillbirth (≥20 weeks’ gestation), neonatal death (≤28 days post-birth), and neonatal unit admission requiring separation of the infant and mother. We will maintain this outcome by reporting a primary perinatal outcome comprising:
   1. Stillbirth ≥ 20 weeks’ gestation (yes/no)
   2. Neonatal death ≤ 28 days post-birth (yes/no)
   3. Severe neonatal morbidity, comprising:
      1. Neonatal seizures (yes/no)
      2. Necrotizing enterocolitis (yes/no)
      3. Hypoxic-ischemic encephalopathy (yes/no)
      4. Birthweight <3^rd^ centile (yes/no)
      5. Bacterial sepsis (yes/no)
      6. Intracranial hemorrhage (yes/no)
      7. Neonatal asphyxia
      8. Cardiac arrest (yes/no)
      9. Requirement for mechanical or non-mechanical resuscitation (yes/no)
      10. Requirement for intubation or mechanical ventilation (yes/no)
3. In the target trial, there were several **secondary maternal outcomes** (see *Target Trial Emulation* Table Sfor full list). As these secondary outcomes are largely accounted for in our primary composite outcome, we will report the following secondary outcomes with treatment effect and 95% confidence intervals (CI):
   1. Need for additional antihypertensives (yes/no)
   2. Progression from gestational hypertension to preeclampsia (yes/no)

Additionally, the following outcomes will also be reported in an exploratory capacity (i.e., with summary statistics only):

1. Individual components of the primary outcome (all reported as yes/no)
2. Hospital admission prior to 37 weeks’ gestation (yes/no)

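### Pregnancy prolongation has a loosely defined start date: read literally it begins before assignment for women dispensed one study drug before 11 weeks (minor)

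*SAP*

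**What the plan says.** The start date of the outcome appears once, in the Target Trial Emulation table, row (E), Emulation column, secondary maternal outcomes: "Pregnancy prolongation (time from first antihypertensive dispensation to birth". The Part One descriptive table has a pregnancy prolongation index row (mean, SD) with no start date.

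Assignment is defined in two places. Row (C) of the table puts it "at point of first dispensation of labetalol or nifedipine during the study period (≥11 weeks’ gestation and ≤36+6 weeks’ gestation". The section on treatment strategy, assignment and follow-up, item 2, says that "women will be ‘randomized’ at the point of first dispensation of either labetalol or nifedipine at or beyond 11 weeks’ gestation".

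The population is "All women with hypertensive disorders of pregnancy (gestational hypertension, chronic hypertension, or preeclampsia) requiring antihypertensive treatment (dispensed labetalol or nifedipine", so chronic hypertension is eligible. The only exclusion for earlier treatment is "Taking both labetalol and nifedipine prior to 11 weeks’ gestation".

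On reporting, the table's note states "Variables denoted with a * are reported with treatment effect and 95% CI, all others are exploratory only and described with summary statistics", and pregnancy prolongation carries the star. The Outcome definitions section introduces its maternal list with "we will report the following secondary outcomes with treatment effect and 95% confidence intervals (CI". That list has two items, additional antihypertensives and progression to preeclampsia. Pregnancy prolongation is not among them.

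**The concern.** In a target trial emulation, eligibility, assignment and the start of outcome time should share one date. Here the outcome's start date is worded more widely than the assignment date. The two coincide for a woman whose first antihypertensive is the assigning dispensation. They need not coincide for a woman already dispensed one study drug before 11 weeks, and she is not excluded.

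Days before assignment cannot be an effect of the drug assigned later, and the pregnancy necessarily continued through them. Counting them lengthens the apparent prolongation of every woman treated earlier. Whether they also distort the comparison depends on whether earlier treatment differs by arm once the weighting and outcome models have been applied. Prior antihypertensive use is not in the SAP's list of selection covariates, nor in the fitted balance tables, so nothing in the plan balances it directly.

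**Working it through.** The SAP gives no figure for pregnancy prolongation, so there is none to reproduce. The check compares the two start dates on example records and then asks what the difference could do to the contrast.

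**Step 1: individual records.** Assume birth at 37+0.

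| Record | Literal rule | From assignment | Excess |
| --- | --- | --- | --- |
| Labetalol at 5+0, next at 11+0 | (37 − 5) × 7 = 224 days | (37 − 11) × 7 = 182 days | 42 days |
| Labetalol first at 30+0, nothing earlier | (37 − 30) × 7 = 49 days | 49 days | 0 days |

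The first record needs only early dispensations of a study drug. The exclusion rule already requires the data to show these.

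A third type of record would be another antihypertensive at 8+0, then nifedipine first at 28+0. It would give (37 − 8) × 7 = 203 against (37 − 28) × 7 = 63, an excess of 140 days. That requires dispensing data on other agents to be used for this variable. Under Data Sources, the dispensing dataset is described as identifying users of the two study drugs only, so this record is possible but not established.

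**Step 2: arm means and contrast.** Let f be the share of an arm with an earlier dispensation and t the mean lead time in days. The arm mean is inflated by f × t. The nifedipine minus labetalol difference is shifted by f_N × t_N − f_L × t_L. The SAP gives neither f nor t, so the values below are assumptions:

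- f = 10% in both arms, t = 7 to 70 days in both: each mean is inflated by 0.7 to 7.0 days and the difference by 0.
- f = 20% nifedipine, 10% labetalol, t = 7, 28 or 70 days: the difference shifts by +0.7, +2.8 or +7.0 days.
- The same shares reversed: −0.7, −2.8 or −7.0 days.

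**Step 3: scale.** With about 7,500 women split 90/10 (6,750 and 750), the smallest difference in means detectable with 80% power at two-sided 5% is roughly SD × √(1/750 + 1/6,750) × (1.96 + 0.84). For assumed SDs of 28, 42 and 56 days this is 3.0, 4.5 and 6.0 days. It ignores any loss of precision from weighting.

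**Step 4: what adjustment may remove.** Chronic hypertension is the most obvious route to early treatment. In the maternal balance table its standardised difference is 0.0536 raw and 0.0046 weighted. A binary variable has SD at most 0.5, so these correspond to at most 0.0536 × 0.5 = 2.7 percentage points raw and 0.0046 × 0.5 = 0.23 points weighted. Suppose earlier treatment were fully determined by chronic hypertension, with a 70-day lead. The weighted shift would then be at most 0.0023 × 70 = 0.16 days. A larger shift needs earlier treatment to differ by arm within hypertension type, on which the SAP is silent.

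**The case against.** The strongest reply is that the phrase is shorthand for the assigning dispensation. The Part One table classifies gestation at the start of treatment from 11+0 with no earlier category. The subgroup section uses nearly the same strata for timing of randomization. Follow-up begins at 11 weeks. All of this suggests that the authors treat the start of treatment and assignment as one event.

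That reading is plausible and stands as a possibility. It is not stated anywhere, and the same outcome list gives some reason for doubt. Disease progression is explicitly anchored to randomization while prolongation is not, and the adjacent item uses the word antihypertensive without limiting it to the two study drugs. Two programmers could derive different variables from this text.

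A reader might go further and infer that the plan will produce a false treatment effect of several days, or that baseline differences between arms show which drug would be favoured. The documents do not support this. The shares and lead times are assumed, and equal values give no shift in the contrast. The raw standardised differences that look suggestive (chronic hypertension 0.0536, preeclampsia 0.1222, comorbidities 0.1745) fall to 0.0046, 0.0058 and 0.0075 after weighting. The 10-point imbalance used for illustration exceeds the raw imbalance these allow: even 0.1745 × 0.5 is 8.7 points.

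It can also be said that no treatment effect may be planned for this outcome. That objection partly stands. The star says there will be one, the Outcome definitions list leaves it out, and the stated contrasts (relative risk and risk difference) do not suit a duration.

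**Conclusion.** The concern holds as an imprecise start date. Taken literally, the definition is wider than the assigning dispensation and adds pre-assignment days for women dispensed one study drug before 11 weeks, 42 days in the worked record. Arm means are then inflated. The contrast is biased only if the share treated earlier or the lead time differs by arm after adjustment.

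The size of any bias cannot be determined from the SAP. Under assumed inputs it runs from 0 to about 7 days in either direction, and it could be well under a day if hypertension type captures most of the difference in earlier treatment. The outcome's reporting status is itself inconsistent between the table and the text. The primary outcomes are not affected. Severity is minor.

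**What to change.** Define pregnancy prolongation as the number of days from the assigning dispensation (first labetalol or nifedipine at 11+0 to 36+6 weeks) to birth, and apply the same definition to the index row in the Part One table. This removes pre-assignment time by construction, whatever the pattern of earlier treatment.

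Reconcile the starred entry in the Target Trial Emulation table with the list under Outcome definitions. If a treatment effect is to be reported, name a measure suited to a duration, such as a difference in mean days. If not, remove the star.

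The cost is one sentence for the definition, an edit to align the two lists, and a date variable that already exists because it defines assignment.

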**ANTICIPATED SAMPLE SIZE**

Our sample will comprise all women with hypertensive disorders of pregnancy (chronic hypertension, gestational hypertension, or preeclampsia) who birthed in Victoria between 2009 – 2020, and were prescribed either labetalol or nifedipine between 11-36 weeks’ gestation. In a blinded review of our data, we have determined our sample size to be approximately 7,500. Of these, approximately 90% received labetalol, and the remaining 10% received nifedipine. Based on this, we are powered to detect an exact difference between groups of ≥3.0% for the maternal primary outcome and ≥5.6% for the neonatal primary outcome.

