| **(F) Causal contrasts of interest** | **Binary Outcomes**  Relative risk (RR) and risk difference (RD) of each outcome (point estimate RR 95% CI) | **Causal comparison:**  *What is the causal effect of exposure to nifedipine during pregnancy on adverse maternal and perinatal outcomes, compared with exposure to labetalol?*  **Estimand = Average treatment effect (ATE)**  Relative risk (RR) and risk difference (RD) of developing each adverse outcome (ATE RR 95% CI).  ***Estimator model*** *–*Doubly robust inverse probability weighting with regression adjustment. |

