3. Total number of dose(s) of allocated antihypertensive drug (mean, SD)
4. In the target trial, there were several **secondary perinatal outcomes** (see *Target Trial Emulation* Table Sfor full list). In our emulation, we will report the following secondary outcomes with treatment effect and 95% confidence intervals (CI):
   1. Preterm birth <37; <34; <32; and <28 weeks’ gestation (yes/no)
   2. Birthweight ≤3^rd^ centile (yes/no)
   3. Neonatal hypoglycemia (yes/no)
   4. Major congenital anomaly as defined by EURO-CAT (yes/no)

Additionally, the following outcomes will also be reported in an exploratory capacity (i.e., with summary statistics only):

1. Individual components of the primary composite outcome (all yes/no)
2. Birthweight <10^th^ centile (yes/no)
3. Mode of birth (spontaneous vaginal, operative vaginal, elective caesarean section, emergency caesarean section)

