**(C) Augmented inverse probability weighted regression adjustment model (IPWRA)**

This is one of the doubly robust methods which combines the IPW selection model with the RA outcome model. This provides two opportunities for correct model specification and may provide valid estimates if only one of the submodels is mis-specified.

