**Combining individual analysis model ATE into the population ATE estimator.**

Probability weighting induces within subject correlation in the outcome in the weighted sample resulting in biased (on the low side) standard errors (SE’s). While a robust SE setting in the analysis model does account for this lack of independence, it does not account for the fact that the propensity score is estimated, rather than known.

Alternatives include:

(i) Bootstrapping, where the propensity score is estimated within each bootstrap sample, and thus the bootstrap estimate of the standard error incorporates sampling variability in the estimated propensity score (BootImpute). ^12^

(ii) BootImpute von Hippel^13^, where the ATE variance estimate is calculated from an ANOVA model, and requires a smaller number of bootstrap samples and imputations.

We will integrate IPW with multiple imputation to calculate the pooled ATE. This will be performed using the BootMI von Hippel method. ^13^

In brief, we obtain B (B=1000) bootstrapped samples from the observational data; for each of the B bootstrapped samples, impute M datasets (M=2); the ATE point estimate is calculated as mean over all B times M complete datasets; a one-way ANOVA model is used to estimate the two variance components (within and between bootstrap samples), which are then used to estimate the standard error and construct associated 95% confidence intervals, incorporating Satterthwaite’s degrees of freedom correlation.

Consideration will be given to using Boot MI percentile, if computationally possible as a sensitivity analysis. In this procedure the first step is to obtain B (B=1000) bootstrapped samples from the observational data; for each of the B bootstrapped samples, impute M datasets (M=20 to 50); a point estimate is then calculated, and a 95% percentile-based confidence interval for the population parameter is generated by taking 2.5% and 97.5% empirical percentiles based upon the mean ATE of the M imputed datasets for each bootstrapped sample. ^12^

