**SOFTWARE**

Analysis will be performed using Stata v18 (StataCorp. 2023. *Stata Statistical Software: Release 18*. College Station, TX: StataCorp LLC). Causal inference will be performed using *teffects* commands (treatment-effects estimation for observational data, see TE-teffects) run within Stata’s multiple imputation suite and TMLE using the *etmle* module^9^ or *TMLE* package in R.

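### For rare secondary outcomes and small subgroups, a by-arm IPWRA outcome model will often have no finite fit in the nifedipine arm, and the SAP has no rule for this

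*SAP*

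**What the plan says.** - **Estimator.** Row (F) of the Target Trial Emulation table gives the contrast as "Relative risk (RR) and risk difference (RD) of developing each adverse outcome (ATE RR 95% CI") and names doubly robust inverse probability weighting with regression adjustment. The section on estimator (C) says: "This is one of the doubly robust methods which combines the IPW selection model with the RA outcome model".
- **Outcome model.** Causal contrasts of interest specifies logistic regression. The section on estimator (B) leaves the covariates to the DAGs, and the text gives no list.
- **Software.** The teffects commands are to be "run within Stata’s multiple imputation suite".
- **Sample.** Under Anticipated Sample Size, "we have determined our sample size to be approximately 7,500" and "approximately 90% received labetalol, and the remaining 10% received nifedipine".
- **Outcomes with an effect estimate.** The outcomes row of the table, Outcome definitions and Causal contrasts of interest limit these to the two primary composites and selected secondaries. The selected secondaries include "Preterm birth <37; <34; <32; and <28 weeks’ gestation (yes/no") and major congenital anomaly. Individual components of the composites get summary statistics only.
- **Pooling.** B=1000 bootstrap samples are drawn and, "for each of the B bootstrapped samples, impute M datasets (M=2"). The point estimate is the mean over all B times M fits, and both ANOVA variance components come from the same fits.
- **Remedies.** Section (A) lists steps for poor propensity overlap. The SAP states no minimum event count, no fallback outcome model and no rule for replicates that fail.

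**The concern.** In an arm-specific logistic model, a covariate level that contains no events makes the likelihood separated, so at least one coefficient has no finite estimate. With 750 women in the smaller arm and a rare outcome, low-prevalence covariates such as multiple pregnancy will often meet this condition, and bootstrap resampling makes it more common.

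Two things are then at stake. First, the mean over 2,000 fits (1000 x 2) is undefined if some fits return nothing. Secondly, fits succeed mainly in resamples that happen to contain more nifedipine events, so averaging only those overstates nifedipine risk and bases the variance on a selected set. With no rule in the SAP, the choice would be made after results are seen.

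**Working it through.** **1. Arm sizes.** 7,500 x 0.90 = 6,750 labetalol and 7,500 x 0.10 = 750 nifedipine.

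**2. The plan's own figures.** The SAP gives detectable differences of "≥3.0% for the maternal primary outcome and ≥5.6% for the neonatal primary outcome" without alpha, power or base rates, so they cannot be reproduced directly. I solved for the base rate with a pooled-variance two-proportion test, two-sided 5%: power = Φ[(d − 1.96·se0)/se1], where se0 is the pooled and se1 the unpooled standard error.
- Maternal, 90% power: d = 3.0 points fits a labetalol rate of about 5.0% (for an increase) or 7.5% (for a decrease). Check at 4.98% v 7.98%: se0 = 0.00861, se1 = 0.01024, (0.03 − 1.96 x 0.00861)/0.01024 = 1.28, power 90%.
- Maternal, 80% power: 7.5% or 9.5%.
- Neonatal, 90% power: 25.8% or 30.5%. At 80% power no base rate gives 5.6 points; the largest detectable difference is (1.96 + 0.84) x √[0.25 x (1/6,750 + 1/750)] = 5.4 points.

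Implied nifedipine events: maternal 34 (750 x 4.5%) to 79 (750 x 10.5%); neonatal 187 (750 x 24.9%) to 236 (750 x 31.4%).

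**3. Events for rarer outcomes.** The SAP gives no rates, so these are assumed: 1% gives 7.5 nifedipine events, 2% gives 15, 3% gives 22.5.

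**4. Number of terms.** The maternal and neonatal balance tables each have 13 non-reference terms: subtype 2, comorbidities 1, parity 1, smoking 1, plurality 1, ART 1, SEIFA 4, age 1, BMI 1. These are propensity terms, used as a proxy for the outcome model.

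**5. Mechanism, one covariate level.** Take multiple pregnancies at an assumed 3.5%: 750 x 0.035 ≈ 26 women. If they carry the average risk, the chance of no event among them is 0.99^26 = 77% at a 1% rate, 0.98^26 = 59% at 2%, 0.97^26 = 45% at 3% and 0.95^26 = 26% at 5%. Other levels add to this, and resampling adds more.

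**6. Simulated bootstrap fits, nifedipine arm of 750, 13 terms.** Smoking and SEIFA shares are from the imputation tables; other prevalences and covariate effects are assumed. Ranges are across several sets of assumptions.

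| Event rate | No finite fit |
|---|---|
| 1% | about 99% |
| 2% | 83–93% |
| 3% | 58–69% |
| 5% | 15–55% |
| 7.5% | 2–21% |
| 28% | 0–1% |

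With only five binary terms the shares are 79% at 1%, 47% at 2% and 5% at 5%.

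**7. Subgroups (sizes assumed, 13 terms).** With 300 nifedipine women: 78% fail at a 6.2% rate and 3% at 28%. With 150: 96% at 6.2% and 23% at 28%. With 75: 80% at 28%.

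**8. Effect of dropping failed fits, compared within the same cohort.** Nifedipine risk rises by about 0.1 point at 5% (0.07 to 0.11), 0.21 at 3% and 0.23 to 0.29 at 2%. At 1% it was about 0.5 point, but only 3 to 5 of 60 simulated cohorts had any usable fit, so that figure is unstable.

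**9. Effect of keeping every fit.** An event-free level drives its fitted probability towards zero, so the averaged risk stays finite. In an unweighted simulation, mean nifedipine risk was 5.05%, 3.06%, 2.11% and 1.19% for true values of 5%, 3%, 2% and 1%. A weighted simulation shifted the RD by about 0.15 point at 1%.

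**10. Alternative.** One weighted logistic model across both arms with shared slopes failed in 6–11% of resamples at 1%, 1% or fewer at 2%, and none at 3% and 5%. It agreed with IPW to within 0.01 point.

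**The case against.** **Scope.** Row (F) might be read as prescribing IPWRA for every outcome. The documents do not support that: the other sections restrict effect estimates, so the rarest components are never modelled. This stands; row (F) is merely worded too widely.

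**The primaries.** A reader might infer that the nifedipine arm is too small for the whole analysis. It is not. The neonatal composite has ample events. The maternal composite may lose fits, but a shift of about 0.1 point is small beside the 3.0-point detectable difference. This stands.

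**Dropping failed fits.** The SAP never says that they are dropped, so bias against nifedipine is conditional and not a stated feature of the plan. This stands. Silence is still a defect, because the mean over all fits needs a rule.

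**Model size.** The 13 terms come from a propensity table, the DAG figures are not available here, and a smaller model fails less. This stands, but five terms still fail in about half of resamples at 2%. Treating renal and autoimmune disease as separate rare terms gives higher failure rates, but the balance tables merge comorbidities into one term, so I do not rely on that.

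**Separate fits by arm.** This is a property of the named command; the SAP does not state it. It is the natural reading of the Software section.

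**Estimators already listed.** IPW, regression adjustment and TMLE appear as potential estimators. That makes the fix easy, but the SAP does not say when one replaces IPWRA.

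**Conclusion.** The point holds for rare secondaries that receive an effect estimate (birth before 28 weeks, and major congenital anomaly if rare) and for the smaller subgroups. At assumed event rates of 1% to 3%, about 60% to 99% of bootstrap resamples have no finite nifedipine-arm fit. The specified mean is then not computable. If failures are dropped, it is biased against nifedipine by about 0.2 to 0.3 point at 2% to 3%; if all fits are kept, the shift is about 0.15 point at 1%. Against a true risk of 1% to 3%, these shifts are large in relative terms.

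In the full cohort the neonatal composite is unaffected and the maternal composite moves by about 0.1 point at 5%. There is no case here for replacing IPWRA in either primary analysis.

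The sizes rest on assumed event rates, covariate prevalences and subgroup sizes, on 13 terms as a proxy, and on by-arm fitting in teffects.

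**What to change.** - Keep IPWRA for the two primary composites in the full cohort.
- In row (F) and section (C), set a minimum event count in the smaller arm, for example about 20, with the exact threshold for the sponsor to fix. Below it, for secondaries and subgroups, use either the IPW estimate the SAP already lists, or one inverse-probability-weighted logistic model across both arms with a drug term and shared slopes, standardised to RD and RR. The latter stays doubly robust, because the weighted score equations for the intercept and drug term set the weighted residuals to zero in each arm. For the very rarest outcomes IPW is safer, as the shared-slope model still failed in 6–11% of resamples at 1%.
- In the section on combining ATE estimates, require the number of failed replicates to be reported, do not average over converged fits only, and switch to IPW if failures are more than trivial.
- List the outcome-model covariates in the text.
- Reword row (F) to match the restricted list of outcomes with an effect estimate.

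The cost is SAP wording and a different command for a few outcomes; standard errors already come from the bootstrap. The downside, for sparse outcomes only, is that covariate slopes cannot differ by drug, or that outcome-model adjustment is given up.
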